## Abstract

**Background:**

Many stroke survivors suffer from sensory impairments of their affected upper limb (UL). Although such impairments can affect the ability to use the UL in everyday activities, very little attention is paid to sensory impairments in stroke rehabilitation. The purpose of this trial is to investigate if sensory re-learning in combination with task-specific training may prove to be more effective than task-specific training alone to improve sensory function of the hand, dexterity, the ability to use the hand in daily activities, perceived participation, and life satisfaction.

**Methods/design:**

This study is a single-blinded pilot randomized controlled trial (RCT) with two treatment arms. The participants will be randomly assigned either to sensory re-learning in combination with task-specific training (sensory group) or to task-specific training only (control group). The training will consist of 2.5 h of group training per session, 2 times per week for 5 weeks. The primary outcome measures to assess sensory function are as follows: Semmes-Weinstein monofilament, Shape/Texture Identification (STI™) test, Fugl-Meyer Assessment—upper extremity (FMA-UE; sensory section), and tactile object identification test. The secondary outcome measures to assess motor function are as follows: Box and Block Test (BBT), mini Sollerman Hand Function Test (mSHFT), Modified Motor Assessment Scale (M-MAS), and Grippit. To assess the ability to use the hand in daily activities, perceived participation, and life satisfaction, the Motor Activity Log (MAL), Canadian Occupational Performance Measure (COPM), Stroke Impact Scale (SIS) participation domain, and Life Satisfaction checklist will be used. Assessments will be performed pre- and post-training and at 3-month follow-up by independent assessors, who are blinded to the participants’ group allocation. At the 3-month follow-up, the participants in the sensory group will also be interviewed about their general experience of the training and how effective they perceived the training.

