The purpose of this pilot randomized controlled trial (RCT) is therefore to investigate if sensory re-learning in combination with task-specific training may prove to be more effective than task-specific training alone to improve sensation of the hand (primary outcome), dexterity, ability to perform daily hand activities, perceived participation, and life satisfaction (secondary outcomes). The results from this study can provide information on how to design a fully powered RCT in the future.

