### Outcome measures and assessors

To be able to evaluate the effects of interventions, outcome measures with good psychometric properties will be used, covering different domains of the International Classification of Functioning, Disability and Health (ICF) [28]. Two occupational therapists, who are blinded to the group allocation and with long experience of stroke rehabilitation and the outcome measures used, will conduct all assessments pre- and post-training and at 3-month follow-up. At the 3-month follow-up, the participants in the sensory training group will also be interviewed regarding their experiences and perceived effects of the training by an interviewer not involved in the training.

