### Data analysis

Descriptive statistics (mean (SD) or median (minimum–maximum)) will be used to characterize the study groups. As this is a new treatment approach, no power calculation can be performed. However, 30 participants can be considered sufficient to include in a pilot RCT within a reasonable time frame. To analyze potential differences between the groups, the Mann-Whitney test (for ordinal data) or independent sample *t* test (for continuous data) will be used. The Wilcoxon signed-rank test or paired *t* test will be used to analyze within-group differences. The level of statistical significance will be set at *p* ≤ 0.05. All calculations will be performed using IBM SPSS Statistics version 22 (IBM Corporation, Armonk, NY, USA).

The interviews of the participants in the sensory group at the 3-month follow-up will be recorded and transcribed verbatim. Data will be analyzed with an inductive content analysis approach [45].

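### Four co-equal primary sensory measures at two visits, tested at an unadjusted 0.05, do not fix a single primary result

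*Protocol article*

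**What the plan says.** The purpose statement that closes the Background treats hand sensation as one primary outcome: the training is meant "to improve sensation of the hand (primary outcome), dexterity, ability to perform daily hand activities", with everything after sensation ranked as secondary.

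The abstract turns that one outcome into four measures. Its list opens with "The primary outcome measures to assess sensory function are as follows: Semmes-Weinstein monofilament" and goes on to name the STI test, the sensory part of the Fugl-Meyer upper-limb scale, and a test of recognising objects by touch. The section on primary outcome measures describes the same four in turn and puts none ahead of the others.

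On timing, the section on outcome measures and assessors says that the two blinded therapists "will conduct all assessments pre- and post-training and at 3-month follow-up". That makes two post-baseline visits, and neither is called primary.

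On analysis, the Data analysis section says: "To analyze potential differences between the groups, the Mann-Whitney test (for ordinal data) or independent sample *t* test (for continuous data) will be used". The threshold follows: "The level of statistical significance will be set at *p* ≤ 0.05". The same section plans within-group tests, states that no power calculation was possible, and justifies 30 participants by what can be recruited in a reasonable time.

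**The concern.** One primary outcome in the purpose becomes four measures at two visits in the methods, and the only stated threshold applies to each test separately. On the natural reading there are eight between-group primary tests, or four if only one visit is used. The article does not say which test carries the primary conclusion, or what is concluded if the monofilament test is significant and the other three are not, or if a difference appears after training and is gone at 3 months.

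This matters because the article does not confine itself to feasibility. The abstract, the Background and the Discussion all state the aim as finding out whether the combined training is more effective than task-specific training alone. With 15 per arm, mixed results across four scales are likely. A chance finding on one scale at one visit could then be reported as a positive primary result, at a false-positive rate well above the 5% that the threshold suggests.

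**Working it through.** **Inputs from the protocol article.** Four primary measures (abstract; primary outcome measures). Two post-baseline visits (abstract; outcome measures and assessors). Level 0.05 per test (Data analysis). 15 per arm (Study design).

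**Assumptions.** Tests are two-sided, since sidedness is not stated. Correlations between scales and over time are not given, so a range is shown. There is no power calculation in the article to reproduce.

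**Step 1: independent tests (upper bound).** The chance of at least one p ≤ 0.05 in k tests under no effect is 1 − 0.95^k.
- k = 4 (one visit): 1 − 0.95^4 = 0.185.
- k = 8 (two visits): 1 − 0.95^8 = 0.337.

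**Step 2: correlated tests.** Simulated multivariate normal test statistics, 1,000,000 draws per setting, two-sided 0.05. For two visits, the correlation between two tests is the between-scale value times the over-time value when both scale and visit differ. The last column counts only false positives favouring the sensory group; for one single test that figure is 2.5%.

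| Tests | Between scales | Over time | Either direction | Favouring sensory group |
|---|---|---|---|---|
| 4 (one visit) | 0.3 | – | 17.3% | 8.7% |
| 4 | 0.5 | – | 15.6% | 7.8% |
| 4 | 0.7 | – | 13.0% | 6.5% |
| 8 (two visits) | 0.3 | 0.7 | 27.7% | 14.1% |
| 8 | 0.5 | 0.7 | 24.8% | 12.5% |
| 8 | 0.7 | 0.7 | 20.9% | 10.4% |
| 8 | 0.8 | 0.9 | 15.6% | 7.8% |

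A separate simulation of 20,000 null trials with 15 per arm and t tests gave 17.5%, 15.5% and 13.3% for four tests, and 27.6%, 25.0% and 21.0% for eight, at between-scale correlations of 0.3, 0.5 and 0.7. Repeating the check with Mann-Whitney tests on discretised scales hardly changed the rates.

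**Step 3: what adjustment would do and cost.** Bonferroni over four tests uses 0.05/4 = 0.0125 each; if the tests are independent the overall rate is 1 − 0.9875^4 = 0.049. Holm uses 0.0125 for the smallest p, then 0.05/3 = 0.0167, 0.05/2 = 0.025 and 0.05. With 15 per arm, a two-sided t test (28 degrees of freedom) has 80% power for a difference of 1.06 SD at 0.05 and 1.29 SD at 0.0125.

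**The case against.** **The gap may be closed elsewhere.** A hierarchy or adjustment is often left to the statistical analysis plan, which is not at hand, and a journal article is condensed. That is fair for the details of a testing procedure, and an unseen plan could add one. But the article does fix its primary measures and its threshold, and as fixed they do not identify a primary result. Which measure and visit are primary is normally settled in the protocol.

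**It is a pilot.** The article says so repeatedly and admits that it is unpowered. The four scales cover different facets of sensation, and carrying several can show which should lead a later trial. Strict family-wise control is not generally expected in that setting. This stands, and it lowers the severity. It does not remove the point, because the stated aim is comparative effectiveness and significance tests are planned.

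**Stronger readings that the article does not support.**
- A reader might infer that one significant test out of eight is declared sufficient. No section says so, and the Data analysis section does not list tests by visit. Eight tests is the natural reading, not a stated rule.
- A reader might infer that a positive result triggers a larger trial. The abstract and the Discussion say only that, if the approach proves efficient, the results can inform the design of one, and the Background says the same without any condition. No go/no-go rule is defined.
- A reader might count every scale at both visits and quote the expected number of chance findings. Most of those scales are secondary, so the count says nothing about the primary outcome.

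**Conclusion.** The point holds at moderate severity. The article fixes four co-equal primary measures at two visits with an unadjusted per-test threshold, and so leaves the primary result undefined.

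Under no effect, the chance of at least one significant primary between-group test is about 13-17% if one visit is tested and about 21-28% if both are. It falls to about 16% for both visits at very high correlation. About half of each figure favours the sensory group.

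The independent-test values, 18.5% and 33.7%, are bounds. It is tempting to say that the error rate is 34% instead of 5%, but the same scale repeated in the same people will not give independent results. Nor should the one-visit and two-visit figures be merged into one range, since they answer different questions. All the correlated figures rest on assumed correlations and two-sided tests. Mann-Whitney tests on short, tied scales may run slightly below 5% each, which does not restore the nominal rate.

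**What to change.** Amend the Data analysis section, before any group comparison is seen, in one of these ways.

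1. **Single primary comparison.** Name one of the four measures at one visit as primary. Report the other three measures and the other visit as supportive, with 95% confidence intervals. The primary test keeps its 5% level and loses no power. The choice of measure and visit is for the investigators; the article gives no ground for preferring either visit.
2. **Exploratory labelling.** In keeping with the pilot design, label all between-group comparisons exploratory, report estimates with confidence intervals, and state that no efficacy claim will rest on any single p ≤ 0.05. The cost is giving up a confirmatory claim that 30 participants were not sized to support.
3. **All four confirmatory.** Only if the investigators want this: name one visit and apply Holm across the four measures. The detectable difference for the smallest p then rises from 1.06 SD to 1.29 SD at 80% power with 15 per arm, which is a real price in a trial of this size.

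Each is a change of wording. None needs more participants, visits or measurements.

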**Discussion:**

The results from this study can add new knowledge about the effectiveness of sensory re-learning in combination with task-specific training on UL functioning after stroke. If the new training approach proves efficient, the results can provide information on how to design a larger RCT in the future in persons with sensory impairments of the UL after stroke.

**Trial registration:**

ClinicalTrials.gov, NCT03336749. Registered on 8 November 2017.

**Electronic supplementary material:**

The online version of this article (10.1186/s13063-018-2628-1) contains supplementary material, which is available to authorized users.

## Background

Stroke is one of the most common causes of impairments, activity limitations, and participation restrictions in adults [1]. More than half of stroke survivors suffer from sensory impairments of their affected upper limb (UL) [2–4], which are characterized by reduced sense of touch, temperature, proprioception, and pain [2]. The impairments affect the ability to discriminate textures, weights, shapes, and sizes, to grasp and manipulate objects without vision, and to perform bimanual tasks in everyday life [3, 5]. The degree of sensory impairments is associated with stroke severity [2, 6] and recovery of motor performance [7].

The sensory impairments of the UL after stroke often lead to long-term problems to use the UL in daily life [8], such as personal care and household and leisure activities [9, 10]. Despite this, very little attention is paid to sensory impairments in stroke rehabilitation. Instead the focus is on motor recovery, exercises for the lower limbs, and mobility [10, 11]. The possible causes of this discrepancy in sensory and motor rehabilitation are limited knowledge of evidence-based sensory interventions among therapists [12, 13] and lack of use of standardized outcome measures [13].

Different interventions to improve the sensory function are described in the literature, such as mirror therapy, thermal stimulation, and intermittent pneumatic compression [14]. Sensory rehabilitation can be divided into either active sensory training (i.e., manual exploration of different textures, figures, and objects with the hand and fingers, and spatial detection of limb position) or passive sensory training including electrical stimulation, thermal stimulation with hot or cold packs, and pneumatic compression [15, 16]. In a study by Schabrun and Hillier [15], passive sensory training was shown to improve grip strength and dexterity, whereas the effect of active sensory training was unclear. However, other studies have reported positive effects of active sensory training [17, 18]. Carey et al. [19] found that an active sensory discrimination training approach after stroke including texture discrimination, limb position sense, and tactile object recognition (i.e., sensory re-learning training) was more effective than passive sensory training, grasping of common objects, and passive movements of the UL. Furthermore, a few studies have reported that a combination of sensory and motor training including fine motor skills [20], or a learning-based sensorimotor program [21], can improve sensory discrimination and motor control of the UL. However, the studies were based on rather few participants [20, 21] and one study lacked a control group [20].

There is evidence that motor training of the UL in terms of task-specific training with repetitive and context-specific tasks including feedback [22] can improve motor performance of the UL [8, 23]. The sensory and motor systems are closely related [16], and both systems are necessary for accurate and precise movements. To improve overall functioning of the UL after stroke, it may therefore be important to focus not solely on motor training but also on sensory training [24]. However, to the best of our knowledge, no previous study has evaluated the effect of sensory re-learning in combination with task-specific training.

The purpose of this pilot randomized controlled trial (RCT) is therefore to investigate if sensory re-learning in combination with task-specific training may prove to be more effective than task-specific training alone to improve sensation of the hand (primary outcome), dexterity, ability to perform daily hand activities, perceived participation, and life satisfaction (secondary outcomes). The results from this study can provide information on how to design a fully powered RCT in the future.

## Methods/design

### Study design

This is a single-blinded pilot RCT with two treatment arms. Thirty persons with sensory impairments of the UL after stroke will be recruited and randomized either to sensory re-learning in combination with task-specific training (*n* = 15) or to task-specific training only (*n* = 15). In the flow chart (Fig. 1) and the SPIRIT figure (Fig. 2), the overall study design is described, which is in agreement with the SPIRIT checklist (see Additional file 1).

**Fig. 1 Fig1:**
[figure not shown]
Flow chart of the study design

**Fig. 2 Fig2:**
[figure not shown]
SPIRIT figure of enrollment, interventions, and outcome measures. Abbreviations: *SWM* Semmes-Weinstein monofilament, *STI*^*TM*^ Shape/Texture Identification, *FMA-UE* Fugl-Meyer Assessment—upper extremity, *BBT* Box and Block Test, *mSHFT* mini Sollerman Hand Function Test, *M-MAS* Modified Motor Assessment Scale, *MAL* Motor Activity Log, *COPM* Canadian Occupational Performance Measure, *SIS* Stroke Impact Scale

### Inclusion of participants

Potential participants will be identified and recruited by physiotherapists and occupational therapists from the Department of Neurology and Rehabilitation Medicine, Skåne University Hospital or from two outpatient health care settings specialized in stroke rehabilitation. Inclusion criteria are as follows: sensory impairments (≤5 points in the Shape/Texture Identification test [25]) of the UL after stroke, ability to grasp and release an object, ability to understand oral and written information, 18–80 years of age, at least 6 months since stroke onset, and ability to walk with or without an assistive device. Exclusion criteria are as follows: sensory impairments in the UL due to other diagnoses than stroke.

First, a letter with information about the study will be mailed to potential participants. One to 2 weeks later, they will be contacted by phone and asked if they are interested in participating in the study. Additional questions about their sensory-related problems of the UL in daily life will also be asked. Eligible and interested participants will then be assessed at the Department of Neurology and Rehabilitation Medicine.

### Randomization

After the baseline assessments when it has been confirmed that the persons fulfil the inclusion criteria, they will be randomly assigned by sealed paper envelopes either to the sensory group (*n* = 15) or to the control group (*n* = 15) by a person not involved in the training.

### Interventions

The training will consist of 2.5 h of group training with two to three participants per session, twice a week for 5 weeks. Each training session will be supervised by one of the two physiotherapists involved in the study, who are experienced in stroke rehabilitation.

### Training for the sensory group

The design of the sensory re-learning is influenced by Carey et al. [19], Yekutiel and Guttman [17], and Rosén and Lundborg [26]. Sensory re-learning is the patient-oriented expression of sensory re-education which traditionally has been used to describe the concept as: “the gradual and progressive process of reprogramming the brain through the use of cognitive learning techniques such as visualization and verbalization, the use of alternate senses such as vision or hearing and the use of graded tactile stimuli designed to maintain and/or restore sensory areas affected by nerve disorder to improve tactile gnosis” [27].

Each training session will consist of 1-h sensory re-learning comprising three 20-min sessions of (1) touch detection to explore different surfaces; (2) touch discrimination to identify different materials, shapes, textures, weights, and temperatures; and (3) tactile object recognition to examine and identify different objects and proprioception. After a 15-min break, the participants will continue with 1 h of task-specific training comprising three 20-min sessions of (1) tying shoelaces, doing buttons, and pulling up a zipper; (2) fine motor training and bimanual tasks such as pouring water into a bottle and using cutlery; and (3) shuffling, dealing, and turning cards and playing board games.

All participants will be informed about the sensory re-learning approach, i.e., to perform repetitive, graded exercises with increased difficulty, attentive exploration of the stimuli, prevention of vision, and continuous feedback of the impaired sensation via vision or the unaffected hand. They are encouraged to reflect on their sensation when having an object in their affected hand, about the characteristics of the object, size, texture, material, and weight. When they are using their affected hand in daily activities, they should also carefully think of the object’s properties. Individualized home exercises once a week will also be performed including follow-ups of the home activities.

### Training for the control group

The training for the control group includes task-specific exercises without any focus on sensory re-learning. The task-specific training will consist of 2-h practicing comprising six 20-min sessions (including a 15-min break) with exercises of (1) daily activities such as tying shoelaces, doing buttons, and pulling up a zipper; (2) fine motor training and bimanual tasks such as pouring water into a bottle and using cutlery; (3) shuffling, dealing, and turning cards and playing board games; but also (4) strength training for the UL with a Theraband; (5) active arm movements such as reaching for objects; and (6) stretching of the UL. The participants will also be encouraged to use their affected UL as much as possible in daily activities at home.

### Outcome measures and assessors

To be able to evaluate the effects of interventions, outcome measures with good psychometric properties will be used, covering different domains of the International Classification of Functioning, Disability and Health (ICF) [28]. Two occupational therapists, who are blinded to the group allocation and with long experience of stroke rehabilitation and the outcome measures used, will conduct all assessments pre- and post-training and at 3-month follow-up. At the 3-month follow-up, the participants in the sensory training group will also be interviewed regarding their experiences and perceived effects of the training by an interviewer not involved in the training.

### Primary outcome measures

#### Semmes-Weinstein monofilament

This is to assess touch detection thresholds [29] of the hand and fingers. The short version (pocket filaments) with five filaments from 0.07 to 279 g will be used (Touch Test® Sensory Evaluators, North Coast Medical Inc.). The touch detection thresholds are scored on a 0 to 5-point scale, where 5 represents the thinnest filament and 0 represents the largest filament. Five different positions of the hand are tested: the fingertip on digits I, II, and V and the thenar and hypothenar regions, yielding a total sum score of 25 points. The pocket filaments have been used previously in stroke studies [30].

